### Statistical Analysis

Results of validity and reliability testing of the community awareness questionnaire developed in phase 2 will be analyzed using both descriptive and analytical statistics. Demographic data will be analyzed descriptively, while the validation and reliability of the questionnaire will be assessed statistically using Pearson correlation and Cronbach α, respectively. Content and face validity will be qualitatively used to avoid question item ambiguity, ensure clarity and relevancy, and ensure that the questions are not judgmental, intrusive, or distressing to target participants [34]. The questionnaire will be administered through an interview setting, with all selected respondents interviewed at 2 points: a preintervention interview and a postintervention interview conducted approximately 4 weeks later (during the intervention study in phase 4).

During the third phase, the questionnaire developed in phase 2 will be used to collect the data on awareness in the general community. All responses to the questions will be given numerical scores based on correct or positive answers. The total score will be calculated, while the mean range will be used to illustrate the distribution and variation of scores. To measure the impact of the intervention, the change in scores (delta change) between preintervention and postintervention assessments will be calculated for each group. The Wilcoxon signed-rank test will be used to compare paired preintervention and postintervention scores within each group. A *P* value of <.01 will be considered statistically significant, indicating improvements in respondents’ knowledge, prevention practices, and health-seeking behavior.

The acceptability test for DEDIKASI-app will be conducted during the third phase, using a survey based on the TAM. A Likert scale will be used as a scoring system. The results from both community members and HCWs will be descriptively analyzed and presented using a frequency table.

Data from the randomized controlled trial in the fourth phase will be analyzed using SPSS version 21 (IBM Corporation). We will conduct a descriptive analysis by calculating the either the mean or median values of the awareness scores and the count of reported common skin disease cases through DEDIKASI-app. The choice between mean or median will depend on the distribution of the scores. We will also use a box plot diagram to visually compare the measurements between the 2 groups.

For assessing the effectiveness of DEDIKASI-app as an intervention for enhancing awareness compared to the control group, we will apply an independent sample *t* test if the data exhibit a normal distribution. If the data distribution is not normal, we will use the Mann-Whitney test. All statistical analyses will be performed at a significance level of .05, with a 95% CI (or using the IQR if medians are used).

Missing data will be described and explored. We acknowledge that incomplete case analysis can introduce bias and will consider appropriate imputation techniques during final analysis depending on the extent and pattern of missingness. We will include the outcomes of all participants (intention-to-treat), regardless of the extent the intervention group used DEDIKASI-app.

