### Phase 4: Randomized Controlled Trial of the Effectiveness of DEDIKASI-App to Increase Early Detection of Skin Diseases Including Leprosy

The fourth phase is an randomized controlled trial aimed to assess the effectiveness of DEDIKASI-app as a strategy to increase awareness and early detection of leprosy and other common skin diseases.

The sample size will be calculated using the following formula for hypothesis testing for 2 population means (2-sided test) [33]:

The following values will be used: level of significance (α)=5%; power of the test (1-β)=90%; population SD (σ)=5; and population variance (σ^2^)=25. The population mean (µ_1_) will be obtained after the awareness study in the second phase; as there was no previous study available, µ_2_ represents the anticipated population mean of the intervention group. Sample size will be calculated afterward; however, we will expect to obtain 600 participants.

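### Within-arm Wilcoxon tests are presented as the measure of the app's impact, and the between-arm test that can measure it is not fixed to one baseline-adjusted estimate with an interval

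*Protocol article*

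**What the plan says.** Everything here is in the protocol article, mostly under Statistical Analysis.

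- **Within-arm tests.** The section states: "To measure the impact of the intervention, the change in scores (delta change) between preintervention and postintervention assessments will be calculated for each group". It continues: "The Wilcoxon signed-rank test will be used to compare paired preintervention and postintervention scores within each group". A P value below .01 is then taken to indicate improvement in knowledge, prevention practices and health seeking. The Abstract also ties significance to the delta change at P<.01.
- **Between-arm test.** For effectiveness against control, the same section plans an independent-samples t "test if the data exhibit a normal distribution. If the data distribution is not normal, we will use the Mann-Whitney test". It does not say whether the tested variable is the post score or the change score, and it names no covariate.
- **Interval.** Results are to be given at the .05 level "with a 95% CI (or using the IQR if medians are used").
- **Data.** Each respondent is interviewed before the intervention and again about 4 weeks later, so a baseline score exists.
- **Status.** Under Current Progress, data collection for the trial has ended and analysis is under way.

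**The concern.** A pre-post test inside one arm asks whether scores rose. It does not ask whether the app raised them. The article itself supplies other reasons for a rise. The same questionnaire is given by interview twice. The Strengths and Limitations section concedes the Hawthorne effect and expectation bias. The Phase 4 section names health campaigns and seasonal trends as outside influences. A gain from any of these that reaches both arms would pass the within-arm rule and be described as impact. Comparing significance between arms does not repair this, because significant in one arm and not in the other is not a test of the difference.

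The between-arm test is the one that can answer the question, and it is loosely fixed. Its variable is open, its target depends on the look of the data, its baseline information may go unused, and its result could be reported with a measure of spread in place of an interval for the effect.

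**Working it through.** **1. Which phase the Wilcoxon tests belong to.** The sentence sits in a paragraph that opens with the third phase. The awareness study of that phase is cross-sectional, and the preceding paragraph places the pre and post interviews in the phase 4 intervention study. The pre-post text can therefore only describe the trial.

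**2. Inputs.** From the Phase 4 section: "level of significance (α)=5%; power of the test (1-β)=90%; population SD (σ)=5; and population variance (σ^2^)=25", with a "formula for hypothesis testing for 2 population means (2-sided test"), and 600 participants expected. Assumed, because the article does not give them: 300 per arm, pre-post correlation r of 0.3 to 0.7, a common gain of 0.5 to 1.0 points, and no clustering.

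**3. The plan's own figure.** The 600 cannot be reproduced, because no difference in means is stated. Solving for the difference that it implies gives (1.960 + 1.282) × 5 × √(2/300) = 1.32 points, or 0.26 SD. The formula is for two independent means, so the trial was sized for the between-arm comparison.

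**4. Within-arm rule with no app effect.** At r = 0.5 the SD of the change is 5 × √(2 × (1 − 0.5)) = 5. For a 1-point gain, z = 1/(5/√300) = 3.46, and Φ(3.46 − 2.576) = 0.81 for a normal-theory test. Simulating the Wilcoxon test itself (2,000 trials per row, equal gain in both arms) gives:

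| Gain in both arms | App arm P<.01, r = 0.5 | App arm P<.01, r = 0.7 | App arm significant, control not, r = 0.5 | Between-arm t at .05, post / change score, r = 0.5 |
|---|---|---|---|---|
| 0 | 1.3% | 1.1% | 1.3% | 5.2% / 5.5% |
| 0.5 | 19% | 36% | 16% | 4.9% / 4.8% |
| 0.75 | 48% | 75% | 26% | 5.3% / 4.3% |
| 1.0 | 79% | 96% | 18% | 4.9% / 5.5% |

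The within-arm result follows the shared gain. The between-arm result does not.

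**5. Precision of the between-arm comparison.** Relative to a t test on the post score, variance is 2(1 − r) for the change score and 1 − r² for ANCOVA. ANCOVA relative to the change score is therefore (1 + r)/2.

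| r | Change score v post | ANCOVA v post | ANCOVA v change |
|---|---|---|---|
| 0.3 | 1.40 | 0.91 | 0.65 |
| 0.5 | 1.00 | 0.75 | 0.75 |
| 0.7 | 0.60 | 0.51 | 0.85 |

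At a true difference of 1.32 points, power is 90% on the post score. On the change score it is 78%, 90% and 98.7% for the three values of r. With ANCOVA it is 92.5%, 96.3% and 99.5%. The unstated choice of variable thus matters by itself: at r = 0.3 the change score is the worse of the two, and at r = 0.7 it is the better.

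**6. IQR against CI.** If scores are normal with SD 5, their IQR is 2 × 0.6745 × 5 = 6.7 points wide at any sample size. A 95% CI for the mean difference with 300 per arm is 2 × 1.96 × 5 × √(2/300) = 1.6 points wide. The first describes people and the second describes the effect, so one cannot stand in for the other.

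**The case against.** The strongest reply is that the article gives the effectiveness question to a direct comparison with control, and repeats that framing for phase 4 in its Results section. Gains equal in both arms cancel there, as the table shows. The article also keeps both surveys within a fixed 4-week window across clusters to limit outside influences. All of this stands. A reader might infer that the effectiveness conclusion rests on the within-arm tests alone, so that shared gains must be counted as app effect. The document does not support that.

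A reader might also infer that the between-arm test ignores the baseline. That is not shown either. The tested variable is unstated and could be the delta change of the Abstract and the Statistical Analysis section, which does use the baseline. What is certain is that neither a t test nor a Mann-Whitney test adjusts for it as a covariate.

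Three further points have weight.

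- Covariate choice is often left to an analysis plan, and an unadjusted randomised comparison is not invalid for lacking it. Baseline adjustment is therefore an improvement, and its absence alone is not an error.
- The gain and the correlation are assumptions. The 79% belongs to a 1-point gain, and half that gain yields 19%. With a 1-point gain the control arm would usually be significant too, so an attentive reader would see the common rise.
- The IQR phrase may be meant as the spread reported with medians. It does not prove that no interval for the effect will appear.

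What remains is that the article attaches the language of impact and improvement to uncontrolled tests, and that it leaves the controlled comparison unfixed.

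**Conclusion.** The concern holds in this form. Within-arm Wilcoxon tests are set up as a measure of the intervention's impact, and they cannot be one. The between-arm test that can serve is planned, but its variable, its target and its interval are not pinned down.

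The size is illustrative. With SD 5, 300 per arm, r = 0.5, no clustering and no app effect, shared gains of 0.5, 0.75 and 1.0 points make the app-arm test significant at .01 in about 19%, 48% and 79% of trials, against about 5% for the between-arm test. These are not false-positive rates of the trial's effectiveness analysis. ANCOVA would cut variance by 25% against either score at r = 0.5. At r = 0.7 the cut is 49% against the post score and 15% against the change score.

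Two limits apply. Cancellation covers only gains equal in both arms. Participants know their arm, so expectation effects that differ by arm remain under any of these analyses. The 5% also ignores clustering by community health center (CHC), which is a separate matter, as is the conflict between the .01 and .05 levels. With only 21 CHCs allocated, chance baseline imbalance strengthens the case for adjustment.

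**What to change.** 1. Report pre and post values in each arm descriptively only, and remove the reading of the Wilcoxon tests as showing impact or improvement.
2. Base the effectiveness conclusion on one between-arm estimate: the difference in mean post score adjusted for baseline score (ANCOVA), with its 95% CI and with CHC clustering handled as that separate point requires. Keep this estimate whatever the distribution of the scores.
3. Delete the IQR as an alternative to the CI. It may stay as a description of spread beside a median.
4. State whether the planned t test or Mann-Whitney test was meant for the post score or the change score, and report that test as a sensitivity analysis.

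No new data are needed, because the baseline scores are already collected. The small downside is timing. Collection has ended and analysis is under way, so the change must be dated and documented, with a statement of whether results by arm had been seen. Keeping the test as now planned as a sensitivity analysis lets readers judge whether the change altered the conclusion.

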**Methods:**

The study will be conducted in four phases: (1) development of DEDIKASI-app, (2) questionnaire development for an awareness study, (3) acceptability testing, and (4) effect measurement of DEDIKASI-app. We will adopt design thinking methodology to develop the app, involving systematic reviews, expert consultations, focus group discussions, and validation of the questionnaire on skin disease awareness. We will recruit 50 members of the community for the awareness and acceptability study and 1 health care worker per community health center to assess their perception of the app. A pilot study will assess the acceptability of DEDIKASI-app among community members and health care workers based on various constructs, with responses categorized as positive, negative, or undecided. The validity and reliability of a newly developed questionnaire on skin disease awareness will be tested, with validity results analyzed qualitatively and reliability measured using Cronbach α. The effectiveness of DEDIKASI-app in improving community awareness will be evaluated through a randomized controlled trial, using total scores, means, and SDs for control and intervention groups. Statistical significance of awareness level changes will be determined by delta change (*P* value), with *P*<.01 considered significant.

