### Phase 2: Development of a Questionnaire for Measuring Awareness of Common Skin Diseases in the Community

The literature review showed the absence of specific instruments for measuring the level of awareness in the general community of early symptoms of common skin diseases. Thus, in this second phase of the study, we aim to develop a questionnaire for measuring awareness in the general community, which will assess common skin disease knowledge, common skin disease prevention, and the intention to seek health services.

The questionnaire will be developed in 2 steps. The first step involves conducting a literature review, consultation with professional experts, and focus group discussions with persons with and without knowledge or expertise in leprosy. Questions will initially be developed in English based on expert judgement and checks by English language experts. Because the study population is Indonesian, the second step will involve translating the questionnaire into the Indonesian language.

The validity and reliability study for the developed questionnaire will be conducted in the subdistrict of Batumarmar, Pamekasan District, East Java Province, ensuring the questionnaire accurately measures the awareness of the community regarding skin diseases and produces consistent results over time and different respondents. The Batumarmar area was chosen because of its variety of geographic and community characteristics, which include rice fields, mountains, and residential areas in both urban and rural settings. Study participants will include experts in leprosy and behavioral sciences (the study supervisor), local key informants, and members of the general community.

The eligibility criteria for the validity and reliability study are as follows: (1) residents living in Batumarmar subdistrict and Pamekasan District; (2) individuals aged 18-65 years; (3) individuals willing to participate and provide informed consent; and (4) individuals able to understand and communicate in Indonesian and Madurese languages. Aside from the results of the validity and reliability test, data on demographical characteristics, such as gender, age, educational level, and occupation, will be included for analysis.

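### A significant pre-post P value, apparently on the total awareness score, is read as improvement in three separate things, one of which (care-seeking behavior) the questionnaire is not said to measure

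*Protocol article*

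**What the plan says.** The Phase 2 section of the protocol article describes a questionnaire "which will assess common skin disease knowledge, common skin disease prevention, and the intention to seek health services".

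The Statistical Analysis section then sets out the scoring: "All responses to the questions will be given numerical scores based on correct or positive answers". It continues: "The total score will be calculated, while the mean range will be used to illustrate the distribution and variation of scores". Change from before to after the intervention is calculated for each group, and "The Wilcoxon signed-rank test will be used to compare paired preintervention and postintervention scores within each group". A P value below .01 "will be considered statistically significant, indicating improvements in respondents’ knowledge, prevention practices, and health-seeking behavior".

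The abstract's Methods paragraph also rests the trial evaluation on the total: awareness is evaluated "using total scores, means, and SDs for control and intervention groups". It adds: "Statistical significance of awareness level changes will be determined by delta change", again at P<.01.

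No domain score and no domain-level test is named anywhere in the article.

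**The concern.** The article fixes in advance what a significant result means, and that meaning goes further than the test can carry, in two ways.

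- **From a sum to its parts.** If the test is on the total, a gain in one domain can produce the significant result alone. The stated rule would still announce improvement in all three.
- **From intention to behavior.** What the Phase 2 section lists as an intention becomes health-seeking behavior in the interpretation.

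A partial effect is plausible in this design. The app delivers information, the second interview comes about 4 weeks after the first, and participants know their allocation (Ethical Considerations). The Strengths and Limitations section itself concedes expectation bias and a Hawthorne effect. Recall of app content, or readiness to give favorable answers, could move the total without any change in what people do. Behavior is the link to earlier detection, so readers are likely to carry that claim forward.

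**Working it through.** **1. The wording side by side**

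| Domain in the Phase 2 section | Term in the interpretation rule | Match? |
|---|---|---|
| Knowledge | Knowledge | Yes |
| Prevention | Prevention practices | Cannot be settled; the items are not shown |
| Intention to seek services | Health-seeking behavior | No |

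**2. The logic.** Write the change in the total as T = K + P + I (knowledge, prevention, intention). The test addresses whether T is centered on zero. T > 0 is compatible with K > 0 and P = I = 0. This holds for any test, threshold or sample size.

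**3. The article's own sample-size figure.** The Phase 4 section gives two-sided α = 5%, power 90%, SD 5 and an expected 600 participants, but no values for the two means. The 600 can therefore be neither reproduced nor refuted. With 300 per arm (assuming equal arms), the formula can only be inverted:

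δ = 5 × (1.960 + 1.282) × √(2/300) = 1.32 points.

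For comparison, differences of 1, 1.5 and 2 points would need 1052, 468 and 264 people in total. The 1.32 is used below only as a gain of plausible size.

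**4. How often a knowledge-only gain triggers the rule.** The sentence belongs to the paired within-group test at .01, so that is the test to examine. Assumptions not in the article: 300 per arm, pre-post correlation ρ of 0.3 to 0.7, independent respondents. The normal approximation is:

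SD of change = 5 × √(2(1 − ρ)); probability = Φ(gain ÷ (SD of change ÷ √n) − 2.576).

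For a gain of 1.32 and n = 300:

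- ρ = 0.3: SD of change 5.92, SE 0.342, Φ(3.86 − 2.58) = 90%
- ρ = 0.5: SD of change 5.00, SE 0.289, Φ(4.57 − 2.58) = 98%
- ρ = 0.7: SD of change 3.87, SE 0.224, Φ(5.90 − 2.58) = about 100%

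A simulation of the Wilcoxon test itself (800 runs per setting; three domains of equal variance, correlated 0.3) counted runs with P<.01 and an upward shift in the total:

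| Gain in knowledge only | ρ = 0.3 | ρ = 0.5 | ρ = 0.7 |
|---|---|---|---|
| 0.66 points | 26% | 36% | 60% |
| 1.00 points | 62% | 79% | 96% |
| 1.32 points | 90% | 97% | about 100% |
| 2.00 points | about 100% | about 100% | about 100% |

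When the two unchanged domains were tested separately at .01, they showed an improvement in at most about 1% of runs (about 0.5% expected by chance).

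With n = 50, the phase 3 sample, a gain of 1.32 triggers the rule in about 15% to 38% of runs. Phase 3 has no second interview, however; the Statistical Analysis section places the pre-post interviews in phase 4.

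**The case against.** Several points on the other side are fair.

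- **The test sentence says scores, not total score.** Use of the total is an inference. It is a strong one, since the total is the only score named in that paragraph and in the abstract, but a domain-wise reading is not excluded. If domains were meant, the article needs to say so.
- **The clause may loosely list what the composite covers.** That is possible, but it is worded as what a significant result indicates, and a reader applying it would report three gains.
- **Prevention.** A reader might infer that two of the three named outcomes lie outside the instrument. The article does not support that: prevention is a listed domain and its items may ask about practices. Only the step from intention to behavior is a documented mismatch.
- **The effectiveness test.** A reader might infer that the trial's main comparison carries the three-part reading. It does not. The comparison with control, later in the Statistical Analysis section, is framed as being about awareness. The faulty sentence belongs to the within-group test.
- **Evidence on behavior.** A reader might infer that the study collects none. The Strengths and Limitations section says that contact with health centers will be monitored and plans cross-checks with objective measures, and cases reported through the app will be counted. None of this is tied to the P value in question.
- **Caution on multiplicity.** The article promises cautious interpretation because multiple outcomes are examined. That concerns many tests; here one test in each group is given three meanings, and general caution does not withdraw a specific rule.
- **Level of detail.** An article may leave domain scores and any adjustment method to the analysis plan. Their absence is not the fault; the stated interpretation is.

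**Conclusion.** The interpretation rule is wrong as written and should be changed. A significant total would support a change in overall awareness within that group and no more, and the questionnaire as described cannot support a claim about care-seeking behavior.

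Under the stated assumptions, a knowledge-only gain of 1.32 points triggers the rule in about 90% to 100% of arms. That range belongs to one chosen gain and is not a ceiling: larger gains trigger the rule more often and smaller ones less. Arm size, pre-post correlation and the absence of clustering by health center are assumptions that move the percentage but not the logic. Equal domain variances and the inter-domain correlation matter only for the separate domain tests, because the SD of the total is held at 5.

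The harm is limited because the between-arm comparison is already framed as awareness and health-center contacts are monitored. Neither corrects the sentence.

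**What to change.** 1. State which score the Wilcoxon test uses. If it is the total, say that a significant result shows a change in overall awareness within that group only, and that effectiveness is judged from the between-arm comparison.
2. Compute the three domain scores and report the between-arm difference with its confidence interval for each, by the same method as the main between-arm comparison. Claim a domain only on its own result. A formal multiplicity procedure over the three is an option, not a necessary part of the correction.
3. Replace *health-seeking behavior* with *intention to seek health services*. Use *prevention score* unless the items do ask about practices.
4. Base any statement about behavior on the monitored health-center contacts.

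The cost is three extra comparisons on data already collected, and a narrower claim. Since the article reports that data collection has finished and analysis is under way, the change should be made before results are reported, and dated as such.

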The study population is the general community located in 21 CHCs of Pamekasan District. The participating CHCs have already been randomly allocated to either the intervention or control group using a computer-generated sequence by an independent statistician. The intervention group comprises Tlanakan, Bandaran, Pademawu, Sopaah, Galis, Larangan Bedung Kadur, Batumarmar, Teja, and Kowel, and the control group comprises Larangan, Talang, Proppo, Panaguan, Palengaan, Pakong, Waru, Tampojung Pregi, Pasean, Pengantenan, and Bulangan Haji. Allocation concealment was ensured by using sequentially numbered, sealed, opaque envelopes, opened only after enrolment of each cluster. Research assistants will enroll participants through door-to-door recruitment*.* To reduce information contamination, we will ensure geographical separation of intervention and control CHCs where feasible. Pamekasan District, located on Madura Island in East Java Province, covers an area of approximately 792 square kilometers, with a population density of around 850 people per square kilometer. The district is divided into 13 subdistricts, with substantial distances between them; for example, the distance between Batumarmar (a northern subdistrict) and Proppo (a central subdistrict) is approximately 25 kilometers, often requiring over an hour’s travel due to rural road conditions. Given this geographic spread and limited daily intervillage interactions, the risk of information spillover between intervention and control clusters is considered minimal. Baseline and postintervention surveys will be conducted within a short period of a fixed 4-week window across all clusters to minimize variation due to external influences such as health campaigns or seasonal trends. Data collectors will follow the arranged schedule based on the study procedure. For eligibility to participate in the study, participants must be a resident of Pamekasan District, especially in the working area of the 21 CHCs; aged 18-65 years; willing to participate in the study and provide informed consent; and an android or smartphone user. The final criterion might not apply to the control group.

Data regarding the effectiveness of DEDIKASI-app as a strategy to increase awareness and early detection of leprosy and other common skin diseases will be collected using the validated questionnaire that will be developed in phase 2.

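### Health centres are randomised, but the between-arm test treats residents as independent, so its P value is too small if scores within a centre are positively correlated

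*Protocol article*

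**What the plan says.** The Phase 4 section states the unit of allocation: "The participating CHCs have already been randomly allocated to either the intervention or control group using a computer-generated sequence by an independent statistician". It gives the setting as follows: "The study population is the general community located in 21 CHCs of Pamekasan District". It treats the centres as clusters, for example when it says that the allocation envelopes were "opened only after enrolment of each cluster".

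The same section plans the sample size with a two-sided formula for two population means, with "level of significance (α)=5%; power of the test (1-β)=90"% and an SD of 5. It then says: "Sample size will be calculated afterward; however, we will expect to obtain 600 participants". No design effect is mentioned.

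The Statistical Analysis section fixes the comparison of arms: "For assessing the effectiveness of DEDIKASI-app as an intervention for enhancing awareness compared to the control group, we will apply an independent sample". The procedure named there is the *t* test, to be used when scores look normal. The fallback is: "If the data distribution is not normal, we will use the Mann-Whitney test". The level is .05, with a 95% CI, or an IQR where medians are used. Outcomes of all participants are to be included by intention to treat. The same section and the Abstract describe the effect of the intervention as the change in score from before to after.

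**The concern.** The randomised unit and the analysed unit differ. An independent-sample *t* test and a Mann-Whitney test both assume that each observation is independent of the others. Residents of one centre's area were assigned together, and their scores may resemble each other more than those of residents elsewhere.

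The article gives reasons to expect this. Phase 3 picks centres to represent urban and rural areas. Phase 4 stresses distance and little daily contact between villages. Phase 1 has health workers at the centres review the self-assessments, so delivery can also differ by centre.

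These are the only between-arm tests named, and they carry the trial's claim of effectiveness. If the ICC is positive, ordinary differences between areas can be reported as an effect of the app more often than the stated level allows.

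**Working it through.** **Inputs from the article.** 21 CHCs, 600 expected participants, SD 5, two-sided α 5%, power 90% (Phase 4); test level .05 (Statistical Analysis).

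**Assumed.** The ICC is not given; the range .001 to .10 is used. Cluster size is taken as m = 600/21 = 28.6, with centres split 10 and 11.

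**The plan's own figure.** The 600 can be neither confirmed nor refuted, because the two means are not stated. Solving backwards with 300 per arm, the detectable difference is 5 × (1.960 + 1.282) × √(2/300) = 1.32 points, or 0.26 SD, with no design effect. By the same formula, a difference of 1 point needs 1052 in total and 1.5 points needs 468.

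**Effect of ignoring clustering.**

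- Design effect: DE = 1 + (m − 1) × ICC
- True type I error of the unclustered test: 2 × [1 − Φ(1.96/√DE)]
- Coverage of the nominal 95% CI: 1 minus that error
- Width of a valid CI relative to the unclustered one: √DE × 2.093/1.960, where 2.093 is the *t* quantile on 19 df
- Effective sample size: 600/DE

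For ICC .05: DE = 1 + 27.57 × .05 = 2.38; 1.96/√2.38 = 1.27; error = .204.

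| ICC (assumed) | DE | True type I error | CI coverage | Valid CI width ÷ unclustered | Effective n |
|---|---|---|---|---|---|
| .001 | 1.03 | .053 | 94.7% | 1.08 | 584 |
| .01 | 1.28 | .083 | 91.7% | 1.21 | 470 |
| .02 | 1.55 | .116 | 88.4% | 1.33 | 387 |
| .05 | 2.38 | .204 | 79.6% | 1.65 | 252 |
| .10 | 3.76 | .312 | 68.8% | 2.07 | 160 |

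**Simulation check.** 8,000 null trials per ICC, 21 clusters of 28 or 29, split 10 and 11. Rejection rates at nominal .05:

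| ICC | *t* test | Mann-Whitney | *t* test on centre means |
|---|---|---|---|
| 0 | .047 | .047 | .047 |
| .01 | .085 | .083 | .050 |
| .02 | .118 | .114 | .053 |
| .05 | .207 | .203 | .053 |
| .10 | .314 | .305 | .051 |

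The rank test is inflated about as much as the *t* test. The test on centre means holds its level.

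**Power.** With 600 participants and the back-solved difference of 1.32 points, a 19-df analysis has power of about 78%, 69%, 51% and 35% at ICC .01, .02, .05 and .10.

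**Number of centres.** As punctuated, the Phase 4 lists show 9 intervention and 11 control centres, or 20. They reach 21 only if the entry Larangan Bedung Kadur is two centres. With 20 centres m = 600/20 = 30, and DE at ICC .05 is 1 + 29 × .05 = 2.45 instead of 2.38, so the inflation is slightly worse and the df would be 18.

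**The case against.** The strongest reply is that the size of the error rests on an ICC that the article does not give. That stands. A reader might infer that the type I error is certain to be far above .05. The documents do not support that: at ICC .001 it is .053 and at .01 it is .083. The between-arm test is not tied explicitly to one score. If it is run on the change from baseline, as the description of impact suggests, the ICC may be lower than for post-intervention scores.

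A reader might also infer that the 95% CI is too narrow whichever test is used. That holds only for the *t* test branch. The Mann-Whitney branch is paired with an IQR, so there only the P value is affected. Nor does the article say that residents of one centre share schools or interviewers, so the argument should not lean on that.

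The article never says outright that the *t* test is run on individuals. This is an inference, but the natural one: the analysis takes in the outcomes of all participants, the sample size formula is unclustered, and centre means are nowhere mentioned.

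The level is itself unsettled. The Abstract uses P<.01 for changes in awareness, while the Statistical Analysis section applies .05 to all analyses. With 2.576 in place of 1.96 in the error formula, the true error is about .02, .09 and .18 at ICC .01, .05 and .10, which is still inflated against .01.

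One defence fails: that clustering may be left to a fuller document. The article names its tests, and a valid plan would have to contradict them. The text on spillover concerns contamination between arms, not correlation within centres.

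**Conclusion.** Wrong as written. The randomised unit is the health centre, and the stated tests treat residents as independent. Any positive ICC makes the P value of either test too small and, in the *t* test branch, the 95% CI too narrow.

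The direction follows from the design; the size depends on the assumed ICC. It is negligible near .001, moderate at .01 to .02, and serious at .05 to .10. The figures also assume about 28.6 participants per centre and 21 centres. Because this comparison supports the trial's main conclusion, it should be corrected before results are reported.

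**What to change.** Replace the *t* test or Mann-Whitney rule in the Statistical Analysis section with an analysis at the level of the randomised unit, and keep the outcome as described. Either of these would do:

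- a *t* test comparing CHC mean change scores between arms (19 df if there are 21 centres); or
- a linear mixed model of the post-intervention score, adjusted for baseline score, with a random intercept for CHC and a small-sample df correction.

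Report the ICC and the cluster-adjusted 95% CI. Reconcile the lists of centres with the stated count of 21, since the df depend on it. State which significance level governs the comparison. Restate the sample size reasoning with a design effect.

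**Cost.** No new data are needed, and the *t* test on centre means is a standard procedure. The Current Progress section says that analysis is under way, so the change and its date should be documented. The price is a wider CI and power below the 90% of the unclustered formula. Data collection has ended, so more recruitment cannot be counted on to offset that loss, and it should be reported openly.
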